### How Our Interventions Will Address the Problem

The Integrated High-Risk Pregnancy Tracking and Management (IHRPTM) program by ARMMAN (Advancing Reduction in Mortality and Morbidity of Mothers, Children, and Neonates)*,* a nonprofit organization, has been improving health-seeking behavior of pregnant women by building capacities of HWs to ensure efficient antenatal and child care, and timely diagnosis, management, and referral of HRPs. The program is designed to address gaps in HRP management through an integrated, comprehensive, multistep, systemic approach for improved identification, tracking, and end-to-end management of HRPs. Its aim is to reduce delayed, complicated, and irrational referrals to tertiary facilities, allowing these facilities to focus on truly critical cases, leading to satisfaction of women and families with HRP conditions. By capacitating, motivating, and handholding HWs, we anticipate the prevention of pregnancy complications among non-HRP women. Integration of different interventions also leads to improvement in quality of ANC services, thereby lowering overall maternal and neonatal mortality and morbidity in the intervention area.

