#### Hypothesis and Outcomes

The program’s impact evaluation will test the following research hypotheses: (1) Does the program, implemented over 18 months, enhance knowledge, skills, and confidence of the ANMs and the MOs to make early diagnosis and manage the 3 HRPs in the intervention arm, compared to usual care arm? (2) Can the capacitated ANMs and MOs translate their knowledge and skills into practice, particularly for early diagnosis and end-to-end management of the 3 HRP conditions in the intervention arm, compared to the control arm? (3) Does the program improve the quality of ANC services in the intervention arm, compared to the usual care arm?

At the system level, the primary outcomes focus on changes in the knowledge and skills of HWs. The first outcome is the net change in correct knowledge and skills of ANMs to manage (treat, counsel, refer, and follow-up) women with any of the 3 HRP conditions (anemia, PIH, and APH) from baseline to end line, comparing intervention and control arms. The second outcome is the net change in correct knowledge and skills of MOs to manage (treat, counsel, refer, and follow-up) women with any of the 3 HRP conditions (anemia, PIH, and APH) from baseline to end line, comparing intervention and control arms. The percentage of correct knowledge and skills for ANMs and MOs will be calculated based on the number of correct responses provided out of a total of 45 questions on the 3 HRPs, administered at baseline and end line surveys.

The system-level secondary outcomes include the net change in the ability of ANMs to correctly identify HRP-related signs and symptoms from baseline to end line, in intervention versus control arm and net change in the ability of MOs to do the same. Other outcomes include changes in the confidence level of ANMs and MOs to manage HRPs between baseline and end line across 2 arms and to document qualitatively whether any systematic barriers reported by district officials at baseline survey were overcome by the end line, by comparing intervention and control arms.

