At the community level, the primary outcome includes net change in the proportion of RDW with any of the 3 HRP conditions (anemia, PIH, and APH) whose problem was resolved prior to delivery and who reported satisfaction with the management of the condition, from baseline to end line, in intervention versus control arm. Satisfaction level of RDW is measured using a 5-point Likert scale on the topics of “attitude and behavior of staff,” “cleanliness and hygiene,” “comfort and care,” and “overall satisfaction with management of HRP condition at the facility.”

The community-level secondary outcomes include net change in proportion of RDW who received the complete ANC package during their last pregnancy*,* from baseline to end line, in intervention versus control arm. Also includes the net change in proportion of RDW who were sensitized about HRPs by ANM or MO during their last pregnancy*,* during baseline and end line, in intervention versus control arm. Other secondary outcomes include net change in the mean gestational month of first diagnosis of 3 HRPs by an ANM*,* from baseline to end line, in intervention versus control arm, and net change in the proportion of RDW diagnosed with any of the 3 HRPs who received protocol-based management or referral from an ANM*,* from baseline to end line, in intervention versus control arm. We also measure the net change in proportion of RDW diagnosed with any of the 3 HRPs, received protocol-based management or referral from MO*,* from baseline to end line in intervention versus control arm.

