### Community-Level Data Collection

RDW who gave birth within the past year, regardless of HRP status, will be surveyed in all the 4 study districts, at baseline and at end line. Some unique features of the RDW tool are documentation of the previous pregnancy, including details of HRP condition (if applicable), as a story in mother’s own words; a picture of the Mother and Child Protection card to supplement with the question-specific data collected from the RDW through interview; ANC details; and HRP-specific detailed questions, where applicable (Table 3; Multimedia Appendix 6).

**Table 3. T3:** Key data collected in the recently delivered women tool.

Data point collected	Details
Pregnancy and delivery details	Age, delivery date, type and place of delivery, outcome of delivery, child’s age, birth weight, term and preterm status, MCP^a^ card availability, and HRP^b^ status
Reproductive history	Children ever born and surviving, and pregnancy terminations
MCP card photo	With details of each ANC^c^ visit, in picture format
Story of recent pregnancy in mother’s own words	Investigators ask the mother to describe about her most recent pregnancy in her own words, from conception to delivery, including details of any HRP, if applicable. The story told by mother is documented here in a text format
ANC characteristics	Number of ANC visits, details of first ANC visit, experience of risk factors, TT^d^ and IFA^e^ usage, supplementary nutrition, and high-risk conditions experienced, including duration of problem and referrals made for the HRP
Delivery and newborn characteristics	Breech presentation, prolonged labor, excessive bleeding, facility stay after delivery, congenital anomalies, and reasons for cesarean section
Details about severe or moderate anemia, PIH^f^, APH^g^, and other HRP conditions experienced by mother in most recent pregnancy (if applicable)	Timing of first diagnosis of HRP and who diagnosed, risk factors associated with the HRP, and management, referral, counseling, and follow-up details related to the HRP condition
Satisfaction	Level of satisfaction with care received if HRP was present
Background characteristics	Literacy, schooling, religion, caste or tribe, occupation, and owning of own mobile phone by the mother

a MCP: Mother and Child Protection.

b HRP: high-risk pregnancy.

c ANC: antenatal care.

d TT: tetanus toxoid.

e IFA: iron-folic acid.

f PIH: pregnancy-induced hypertension.

g APH: antepartum hemorrhage.

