Given the low prevalence of PIH and APH (around 5%), with 1% margin of error, our study (2000 RDW per arm) is adequately powered at 95% (a conservative estimate). With a higher margin of error (say 1.5%), although the required sample size per arm will reduce to 821, the power of the study will fall below 95%, and the anticipated number of RDW with PIH and APH would be too small to compare (approximately 70‐130 per arm). This would result in high CIs, making HRP-specific impact evaluation a challenging task.

As different respondents will be surveyed at baseline and end line, there is no risk of data attrition. However, since HRP conditions data in this study is relying on self-reports by RDW and expected low prevalence of PIH and APH conditions (around 5%) in India, nonparticipation by RDW with these conditions could compromise the statistical power of the study. To overcome this problem, we have set a narrow margin of error (1%, ie, prevalence could range between 4%‐6%) for baseline and end line estimates in each arm. Our sample size calculation also accounts for a 10% nonresponse rate per arm at both baseline and end line. To increase the effective prevalence of the APH condition, the inclusion criteria for this condition encompass APH, placenta previa, and abruptio placenta. With recent estimates in India showing an increase in prevalence of PIH to 11% [43], while moderate or severe anemia was stagnant at around 26% [39], we are confident of including sufficient RDW with these 2 conditions. Nevertheless, if the prevalence of any of the 3 HRPs falls below 4% at baseline or end line in either arm, the statistical power of the study for that HRP condition will be compromised. We acknowledge this as a limitation of the study.

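### The primary community outcome is a proportion among women who report one of three HRPs, and the programme aims to change who is detected, so the DiD can move without any change in management

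*Protocol article*

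**What the plan says.** The primary community outcome, in the protocol article under Hypothesis and Outcomes, is the "net change in the proportion of RDW with any of the 3 HRP conditions (anemia, PIH, and APH) whose problem was resolved prior to delivery". Satisfaction with how the condition was managed is required as well, and the comparison is intervention versus control. Study Design repeats this denominator.

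How a woman comes to count as having an HRP is described elsewhere. Sample Size of the Quantitative Surveys says "since HRP conditions data in this study is relying on self-reports by RDW". The tool in Community-Level Data Collection adds "a picture of the Mother and Child Protection card to supplement with the question-specific data collected from the RDW through interview", and its HRP module asks for "Timing of first diagnosis of HRP and who diagnosed, risk factors associated with the HRP".

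The programme is meant to act on detection and awareness. Its stated purpose is "improved identification, tracking, and end-to-end management of HRPs". The first hypothesis asks whether health workers become better able to "make early diagnosis and manage the 3 HRPs in the intervention arm, compared to usual care arm". A secondary outcome is the "net change in proportion of RDW who were sensitized about HRPs by ANM or MO during their last pregnancy".

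Against non-random allocation, Study Design offers near-matching on covariates such as age, parity, caste and literacy, followed by covariate-adjusted DiD. Data Analysis treats the descriptive DiD for each indicator as the causal effect of the intervention.

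**The concern.** Membership of the denominator is something the programme tries to change, in the intervention arm and only after baseline. DiD removes fixed differences between arms and changes common to both. It does not remove a change in case mix specific to one arm and one period. Matching and adjustment on demographic covariates address baseline imbalance; they do not undo selection that the intervention itself causes.

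Milder or earlier cases that would otherwise have gone unnoticed can raise the proportion resolved. Harder cases, or a shift from anemia towards PIH and APH, can lower it. Either way, a change in who is counted would be reported as a change in how women were managed. The secondary outcomes on protocol-based management or referral by an ANM or MO, which are taken among women diagnosed with an HRP, are exposed to the same selection. The complete ANC package and sensitization outcomes use all RDW and are not. The findings are meant to inform scale-up to 75 districts, so it matters which effect has been shown.

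**Working it through.** **The plan's own figure.** The only sample-size calculation is a precision formula for a prevalence, n = z²p(1−p)/e². With p = 0.05, e = 0.01 and 95% confidence, n = 1824.7, which reproduces the stated 1825. It assumes 5% PIH in both arms at both surveys, so it allows for no detection shift, and it says nothing about the proportion resolved.

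**Inputs from the protocol.** 2000 RDW per arm per survey. Anticipated cases: anemia 400–500, APH 120–200, PIH 100–340. The lower ends sum to 620 before overlap. With about 1000 of the 2000 expected to have none of the three, about 1000 would have at least one. I use D0 = 620 to 1000 cases per arm and survey.

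**Assumed, because the protocol gives no value.** Resolved-and-satisfied rate p0 = 50% among women already detected; extra detected cases as a fraction f of D0, in the intervention arm at end line only; their rate px; true effect on management zero.

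**Formulas.**
- End-line intervention proportion: p1 = (p0 + f·px)/(1 + f).
- False DiD = p1 − p0, the other three cells being unchanged.
- SE = √[3·p0(1−p0)/D0 + p1(1−p1)/D1], with D1 = D0(1 + f) and no design effect.

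**Results.**
- f = 20%, px = 80%: (0.50 + 0.16)/1.20 = 0.55, so the DiD is +5.0 points.
- f = 20%, px = 20%: (0.50 + 0.04)/1.20 = 0.45, so the DiD is −5.0 points.
- f = 10%: ±2.7 points. f = 30%: ±6.9. f = 50%: ±10.0.
- px = 50%: the DiD is 0 for any f.
- SE at f = 20%: 3.9 points with D0 = 620, 3.1 with D0 = 1000. The chance of a nominally significant result with no management effect is then 25% and 37%, against 5%. Clustering by PSU would widen the SE and lower these percentages, but would leave the bias as it is.

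**Condition mix alone.** If anemia resolves at 60% and PIH and APH at 30% (assumed), 20%–50% more detected anemia moves the pooled outcome by +1.2 to +3.0 points; 20%–50% more PIH moves it by −0.6 to −2.0.

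**How candidate checks behave with care unchanged.** Per 100 RDW, take 30 detected at 50%, then 6 more at 80%.
- Primary: 15.0/30 = 50% becomes 19.8/36 = 55%.
- Resolved and satisfied / all RDW: 15.0 becomes 19.8.
- HRP not resolved and satisfied / all RDW: 15.0 becomes 16.2. Both shares rise, which is the sign of extra detection; either one alone misleads.
- Standardising to condition mix: if the 6 added cases have the same mix as the 30, the +5 points remains.
- Trimming the 6 excess cases: removing 6 successes gives 13.8/30 = 46%; removing 6 failures gives 19.8/30 = 66%. The bounds on the DiD are −4 to +16 points. They include zero, so the apparent gain would correctly not be credited to management.

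**The case against.** The strongest reply has four parts.

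**Detection is part of the intended effect.** Hypothesis 2 tests early diagnosis together with management, so some of what looks like confounding is programme benefit. That stands, but this denominator does not credit detection: finding harder cases lowers it. A combined effect is a legitimate result if it is reported as one.

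**The plan already has condition-specific results and detection indicators.** The survey is sized to give indicators for each HRP by arm, and Data Analysis applies DiD to early diagnosis. These would help expose a mix shift, but the protocol does not tie them to the interpretation of the primary outcome, and they do not show a severity shift within a condition.

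**The rest belongs to the SAP.** The covariate list is introduced as examples and a locked plan is promised. Still, the denominator and the causal reading of the DiD are fixed in this article, so this is a stated choice and not an omission.

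**The shift may be small.** The Introduction reports that nearly all workers diagnosed the anemia and PIH scenarios correctly; the anemia criterion is moderate or severe, which limits mild additions; and 30%–44% of pregnant women would be reached partly or not at all. All of this limits the size. On the other side, the same Introduction reports that only 31% of workers screened, and only for 10 of 16 common conditions, and Table 1 shows 32.9%–42.3% of women with at least 4 ANC visits, so field detection has room to rise.

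Three stronger readings are tempting. A reader might infer that the outcome is defined as self-reported, detected HRP; its wording says only that the woman has the condition, and dependence on detection follows from how status is collected. The card does not break that dependence, because it too records what care found. A reader might infer that the design is biased towards benefit; the sign is undetermined. And a reader might extend the point to the "net change in the mean gestational month of first diagnosis of 3 HRPs by an ANM"; that is itself a detection outcome, so the charge of mixing detection with management does not apply to it.

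**Conclusion.** The concern holds as a structural weakness in how the primary community outcome will be read. Following the plan as written can attribute a change in who is detected to better management. For this to happen, the programme must shift detection or reporting differentially, and the added cases must resolve at a different rate; if they resolve at the same rate there is no bias. Neither the direction nor the size can be derived from the protocol. Under the assumed rates, a 10%–50% rise in detected cases with a 30-point difference in resolution moves the DiD by 2.7 to 10.0 points either way, comparable with or larger than the simple standard error of 3 to 4 points. These figures show that the problem can matter; they are not a forecast.

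**What to change.** Keep the primary outcome and prespecify beside it:

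- (a) the DiD in the share of all RDW reporting each HRP, by condition;
- (b) resolved-and-satisfied / all RDW, and HRP not resolved-and-satisfied / all RDW, always read as a pair;
- (c) the primary DiD by condition and standardised to the pooled baseline condition mix, plus severity or gestation at diagnosis where recorded, stating that condition mix alone does not remove a severity shift;
- (d) if (a) shows a differential change in detection, trimming bounds on the primary DiD that remove the excess detected share. These assume that the programme moves detection in one direction only. The theory of change also expects a lower HRP burden, so state that assumption.

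Attribute the primary result to better management only if (a) shows no material differential change, with materiality defined in advance, or if the bounds in (d) exclude zero. Otherwise report a combined detection-and-management effect. Agreement of (b) and (c) with the primary should not serve as the test: in the worked example, resolved / all RDW and the standardised DiD both rise with care unchanged.

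Treat hemoglobin from the card photographs as supportive only, reported with the share tested in each arm and survey, because testing is also a programme target.

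The survey already covers RDW regardless of HRP status and photographs the card, so no new fieldwork is needed. The cost is some extra analysis, entry of card data if used, and a less sharp headline claim.

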## Methods

### Study Design

The study adopts a “matched, before-after quasi-experimental design with a control (usual care) arm,” as a randomized control study design is not feasible for this kind of system and community-based implementation study. Both qualitative and quantitative data will be collected at the system and community levels, respectively, during baseline (prior to implementation of interventions) and end line (after 18 months of interventions)*,* in the intervention and control arms. The program’s effectiveness at the system level will be evaluated by assessing the capacity of ANMs and MOs to diagnose and manage the 3 HRPs and at the community level by measuring the proportion of RDW with any of the HRP conditions, whose HRP problem got resolved prior to delivery and who were satisfied with the care they have received for the HRP condition*.* Effectiveness of the program through quantitative indicators will be analyzed using the difference-in-difference (DiD) technique.

However, keeping in view the quasi-experimental design of this study, to control for potential baseline differences between intervention and control arms due to nonrandom allocation, we will lock the analysis plan by prespecifying primary outcomes and covariates of the quantitative data. Prior to advanced analyses, we will implement near-matching of intervention and control data on key covariates, such as age, parity, caste, and literacy. In addition, during the main analysis stage, we will apply DiD models with covariate adjustment to further control for any residual imbalance and to strengthen causal inference.

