### Duration of Interventions and Justification for Creating a Usual Care Arm

In 2 intervention districts, the IHRPTM program will be implemented district-wide for 18 months, starting June-July 2024 and ending February-March 2026. The 18-month duration is necessary, as the introduction of different interventions in both the intervention districts requires 3‐6-month time. Also, for converting system level changes into outcomes is a time-consuming process [35]. Given the relatively short implementation period, we are not proposing a midline evaluation. However, the uptake, quality, and coverage of interventions will be continuously monitored through a robust monitoring system. Dipstick studies will be conducted depending upon the need. Any mid-course corrections will be based on findings from the baseline, monitoring data, and dipstick studies.

In the usual care arm, HWs will receive routine capacity-building sessions conducted by the state and the national governments. Pregnant women in both arms will have access to antepartum, intrapartum, and postpartum care programs provided by the state and the national governments. It implies that while general system strengthening interventions are provided in both the arms, the IHRPTM interventions are the only additional interventions confined to the intervention arm. At the community level, the IHRPTM program does not directly work with pregnant women in either arm. The control arm was included to isolate the effect of the IHRPTM interventions from the general system strengthening activities and to assess whether IHRPTM interventions had any incremental effect or value addition beyond what general system strengthening interventions alone can achieve. Thus, this study design ensures ethical equity while also allowing us to isolate the incremental effect of the IHRPTM program interventions by comparing changes in outcomes that go beyond improvements expected from broader system strengthening efforts.

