RDW^a^	Personal interview	Woman aged 15‐49 years, have had delivery during the past 1 year from the date of survey Details of such woman are available with ASHA^b^, AWW^c^, and ANM^d^ in the sampled PSU^e^ or woman was identified through snowballing technique from an interviewed RDW RDW who is resident of nonsampled PSU but had delivery in sampled PSU in past 1 year and is willing to participate in survey	All those who do not give consent to participate in the survey RDW listed by ASHA, AWW, and ANM, but not available for interview on days of survey Had delivery just within 3 days of survey Maternal deaths and RDWs with severe illness and unable to participate in interview
District officials and Specialist gynecologists	IDI	Currently serving in the stated position in the survey district	With less than 1 year of experience in the current position, in the survey district Who do not give consent to participate in the survey
Medical officer and ANM	SSI	Currently serving in the stated position in the sampled PHC^f^ and HSC^g^	With less than 1 year of experience in the current position in sampled PHC and HSC Who do not give consent to participate

a RDW: recently delivered women.

b ASHA: accredited social health activist.

c AWW: anganwadi worker.

d ANM: auxiliary nurse midwife.

e PSU: primary sampling unit.

f PHC: primary health center.

g HSC: health subcenter.

Using the above-stated survey design, tools, and inclusion and exclusion criteria, data for the baseline survey component of the impact evaluation of the IHRPTM program were collected during June-October 2024. Baseline qualitative data from system stakeholders were collected by ARMMAN researchers from 4 districts during June-August 2024. Baseline quantitative data were collected from >4000 RDW by around 75 female investigators and supervisors, during September-October 2024, from 200 PSUs, spread across 4 districts and 2 arms.

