### Triangulation of Mixed Methods Data

As part of the impact evaluation, one of the hypotheses being tested is “‘whether capacitated ANMs and MOs are able to translate their knowledge and skills to manage HRPs into practice.” This hypothesis will mainly be tested by triangulating both the datasets on the listed themes and indicators, particularly, during the end line (Table 5).

**Table 5. T5:** How qualitative and quantitative datasets will be triangulated and integrated?

Theme or indicator	System level data (qualitative)	Community level data (quantitative)
Training and handholding of ANMs^a^ and MOs^b^ on HRPs^c^	Early diagnosis of HRPs reported by ANMs or MOs Improved knowledge and skills to manage HRPs by ANMs and MOs Improved confidence to manage HRPs	Proportion of HRPs diagnosed in the first trimester Protocol-based management of HRPs Protocol-based referral of HRPs Proportion of unnecessary or irrational referrals
Motivation and satisfaction of ANMs and MOs	Digital tools facilitating improved counseling and follow-up of women with HRPs by ANMs and MOs	Proportion of mothers with HRPs counseled and followed up by ANMs and MOs Proportion of mothers with HRPs highly satisfied with management and referral practices of ANMs and MOs
Quality ANC^d^	Improvement in quality of ANC services reported by ANMs and MOs	Proportion of mothers whose weight, hemoglobin, and blood pressure were collected at least 4 times in pregnancy Proportion of mothers who received complete ANC package of services
Facilitators and barriers to HRP management	Specific nuances of facilitators and barriers to HRP management reported by system stakeholders	Proportion of mothers with HRPs using public health facilities for management Proportion of mothers using public health facilities for ANC, delivery, and PNC^e^ care

a ANM: auxiliary nurse midwife.

b MO: medical officer.

c HRP: high-risk pregnancy.

d ANC: antenatal care.

e PNC: postnatal care.

To operationalize triangulation as a methodological practice, the study will use structured integration matrices, defined timelines, and clearly delineated roles. The process will take place during the end line analysis phase (March-June 2026), once both qualitative and quantitative datasets have been collected and validated.

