## Results

The impact evaluation protocol and the protocols for 6 HRP conditions were vetted by the government of UP in May-June 2024. In the 2 intervention districts of Sambhal and Shravasti, in June-July 2024, implementation of listed interventions started in a phased manner, and these interventions will continue for 18 months (until March 2026), in collaboration with district health officials. By November 2024, in the 2 intervention districts, the following interventions had been introduced: (1) protocols on 6 HRP conditions; (2) training of ANMs, MOs, specialist gynecologists, staff nurses, and community health officers on these protocols; and (3) a digital learning tool and a WhatsApp-based support system for ANMs. Baseline data from system stakeholders and community data from recently delivered women were collected during June-October 2024. From November 2024 to October 2025, the listed interventions will continue in the 2 intervention districts, and baseline data from both arms are being analyzed. By November 2024, all the ANMs, MOs, specialist gynecologists, staff nurses, and community health officers of 2 intervention districts were trained on 6 HRP protocols, the learning app for ANMs on the 6 HRPs, and the WhatsApp support system for real-time clarification of doubts by the ANMs (tech plus touch approach) was also introduced. The tracking and data integration system for improved tracking of the HRPs by health facilities at different levels of public health care system is yet to be introduced.

The proposed interventions, designed, developed, implemented, and evaluated using a tech plus touch approach, will capacitate HWs at different levels to make early diagnosis of the HRPs and provide protocol-based management of the diagnosed condition. The findings of the study will identify issues that require need-based planning to ensure quality ANC, delivery, and HRP care services by public health care system, and particularly the ANMs and MOs, who work at the grassroots. At the policy level, findings of the study will provide cues on facilitators and barriers to pregnancy care services at the block and district level, for necessary corrections. The study intends to make an important contribution by evaluating the usefulness and effectiveness of the proposed program and suggesting further improvements or modifications when scaled up across the entire state of UP, a region that is larger than many European countries.

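### The women's baseline was fielded after the programme started and the end line look-back reaches back before roll-out was complete, so a DiD by survey round understates the full-exposure effect

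*Protocol article*

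**What the plan says.** The Study Design section places the two survey rounds "during baseline (prior to implementation of interventions) and end line (after 18 months of interventions". The dates are given elsewhere in the article:

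- **Programme period.** The section on duration of interventions has the programme "starting June-July 2024 and ending February-March 2026". The Results section says that "in June-July 2024, implementation of listed interventions started in a phased manner, and these interventions will continue for 18 months (until March 2026".
- **Health-worker baseline (Survey Design).** "Baseline qualitative data from system stakeholders were collected by ARMMAN researchers from 4 districts during June-August 2024".
- **Women's baseline (Survey Design).** "Baseline quantitative data were collected from >4000 RDW by around 75 female investigators and supervisors, during September-October 2024".
- **Roll-out (Results).** Protocols, training, the learning app and the WhatsApp helpline were in place by November 2024. The tracking system was still outstanding.
- **Who is surveyed (Community-Level Data Collection).** "RDW who gave birth within the past year, regardless of HRP status, will be surveyed", at both rounds.
- **End line.** No fieldwork date is given. Triangulation takes place "during the end line analysis phase (March-June 2026", after both datasets have been collected and validated.
- **Model (Data Analysis).** The DiD as described uses arm and survey-round indicators with covariates. It has no term for when a woman was pregnant relative to the programme.

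**The concern.** A DiD by survey round takes the first round as unexposed and the second as exposed. On the stated dates neither holds cleanly in the intervention districts.

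The women's baseline was fielded wholly after the stated start. The Rationale section places the digital tools 2-3 months after initiation, which is about August-October 2024 and overlaps that fieldwork. The health-worker baseline overlaps the start. This matters for the system-level primary outcomes because the theory of change expects about a 10% immediate knowledge gain from classroom training, so anyone trained before the interview would already carry it. Table 2 plans 8-10 ANMs and 4-5 MOs per district, or 16-20 and 8-10 in the intervention arm, so a few such respondents would count.

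At end line, the one-year look-back brings in pregnancies that began from about mid-2024. The theory of change expects community impact only after 12-18 months of consistent protocol use. A weak or null result from a pilot meant to inform state-wide scale-up could then be read as programme failure when it partly reflects incomplete exposure. The limitations in the Discussion mention neither overlap.

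**Working it through.** **The plan's own figure, 18 months.** Count months from 1 January 2024 = 0, so that 1 June 2024 = 5, end July 2024 = 7, 1 February 2026 = 25, 1 March 2026 = 26 and end March 2026 = 27. June-July 2024 to February-March 2026 spans 25 − 7 = 18 to 27 − 5 = 22 months, so 18 fits only the shortest reading. With the Results section's end in March 2026, the minimum is 26 − 7 = 19. Counting 18 months back from March 2026 gives 26 − 18 = 8 to 27 − 18 = 9, that is, a start during September 2024, when the women's baseline began.

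**Inputs for exposure.** From the article: start in June-July 2024 (t = 5, 6 or 7), women's baseline in September-October 2024 (midpoint S = 9), roll-out in place by November 2024 (c = 10 or 11), a 12-month look-back, and exclusion of deliveries within 3 days of the survey (0.1 month). Assumed: births spread evenly over the look-back, 9-month gestation, and end line fieldwork in February-March 2026 (S = 26), varied from January (S = 24.5) to April-May 2026 (S = 28).

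**Baseline.** Share of sampled deliveries after the start = (S − t − 0.1)/11.9.

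- t = 5: 3.9/11.9 = 33%
- t = 6: 2.9/11.9 = 24%
- t = 7: 1.9/11.9 = 16%

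Most of these women had only late pregnancy after the start. Averaging max(0, delivery − t)/9 over all sampled births by simulation gives 7.2%, 4.1% and 1.8% of gestation time.

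**End line.** Share conceived before roll-out was complete = [12 − (S − c − 9)]/11.9.

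| Fieldwork | c = 10 | c = 11 |
|---|---|---|
| January 2026 | 6.5/11.9 = 55% | 7.5/11.9 = 63% |
| February-March 2026 | 5/11.9 = 42% | 6/11.9 = 50% |
| April-May 2026 | 3/11.9 = 25% | 4/11.9 = 34% |

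For February-March 2026, the whole first trimester preceded roll-out in 2/11.9 = 17% to 3/11.9 = 25%. This bears on the secondary outcome of gestational month at first diagnosis. The mean share of gestation after roll-out, by simulation, is 88% (c = 10) or 83% (c = 11).

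**Net contrast.** End line exposure minus baseline exposure:

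- Least favourable: 0.830 − 0.072 = 0.76
- Most favourable: 0.882 − 0.018 = 0.86

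If the effect is proportional to exposure, the DiD estimates 76-86% of the full-exposure effect. The sample needed for equal power rises by 1/0.863² = 1.3 to 1/0.758² = 1.7. The end line share of the loss is 0.170/0.242 = 70% in the least favourable case and 0.118/0.136 = 87% in the most favourable. With other fieldwork dates the contrast is 0.67-0.79 (January: 0.737 − 0.072 to 0.803 − 0.018) or 0.85-0.94 (April-May: 0.924 − 0.072 to 0.956 − 0.018).

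These figures count any time after the start as exposed at baseline and any time before full roll-out as unexposed at end line. With a phased start, both conventions lean towards a larger loss.

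**The case against.** The strongest reply is that the stated question is the effect of a programme implemented over 18 months, and that the duration section openly allows 3-6 months for introducing the components. An all-women DiD that includes the ramp-up answers that question. This stands, and it is why that analysis should remain the main one. It does not repair the definition of baseline, and it does not tell readers how far the estimate falls short of the effect under full exposure.

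Three stronger readings are tempting, and the documents do not support them:

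- **That ANMs and MOs were trained before their baseline interviews.** No training date is given beyond completion by November 2024. The Rationale section says that the ANMs were trained within a few days, so interviewing first and training afterwards fits every stated date. Contamination here is possible, not shown.
- **That 16-33% of baseline women were treated.** That share only counts deliveries after the start. Roll-out was phased, exposed gestation time is about 2-7%, and the article itself expects 30-44% of women to be reached partly or not at all because they use private or NGO care.
- **That end line women who conceived before November 2024 were unexposed.** With February-March 2026 fieldwork, about 83-88% of end line gestation time still follows roll-out.

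Dropping women from the main analysis would also be costly. Losing half of the end line would cut the 100-340 expected PIH cases per arm to about 50-170 and the 120-200 APH cases to about 60-100. The sample-size section already regards about 70-130 as too few to compare. Excluding trained health workers outright could empty a small intervention-arm baseline.

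**Conclusion.** The concern holds in a limited form. The article contradicts itself on whether baseline preceded implementation. The contradiction is certain for the women's survey; for the health-worker interviews only the overlap in dates is certain. The look-back also leaves a substantial share of end line pregnancies starting before roll-out was complete: about 42-50% under February-March 2026 fieldwork, and 25-63% over January-May 2026.

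The consequence is moderate attenuation, to roughly 76-86% of the full-exposure effect under February-March 2026 fieldwork, and it arises mainly at end line. This rests on even births, a 9-month gestation, an inferred fieldwork date and a beneficial effect proportional to exposure; none of these is stated in the article. If the tracking system counts as part of roll-out, incomplete exposure at end line is larger. The overrun on 18 months is an inconsistency to correct, with no separate analytic consequence beyond leaving the start date unclear.

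**What to change.** 1. **Reconcile the dates.** Study Design, the duration section, Survey Design and Results should agree on when implementation started, what baseline means for each survey, and whether the period is 18 months. State the end line fieldwork dates, and whether the tracking system counts towards complete roll-out.
2. **Keep the all-women DiD as the main analysis and prespecify an exposure-defined DiD beside it.** Use delivery date, and a conception date estimated from delivery date and term status, all of which the women's tool already collects. Restrict baseline to deliveries before the first programme training, and end line to conceptions after roll-out was complete. Apply the same calendar cut-offs in both districts of each matched pair (Shravasti-Gonda, Sambhal-Budaun).
3. **Report each intervention-arm ANM's and MO's training date relative to the baseline interview.** If any were trained first, add a sensitivity analysis without them and leave the main analysis intact.

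The cost is plan wording plus date fields that exist or should be held by the implementing organisation. The restricted DiD loses about a sixth to a third of baseline women and up to about half of end line women (more if fieldwork is as early as January 2026). It will therefore be less precise, especially for PIH and APH, and should be read as supportive.
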